## Abstract

Insomnia is a common health problem in the general population. There are different ways to improve sleeping habits and quality of sleep; however, there is no clinical trial using transdermal neurostimulation to treat individuals with symptoms of insomnia in Asia. This gives us the impetus to execute the first study in Asia which aims to evaluate the efficacy of Electrical Vestibular Stimulation (VeNS) on individuals with insomnia in Hong Kong. This study proposes a two-armed, double-blinded, randomized, sham-controlled trial including the active VeNS and sham VeNS group. Both groups will be measured at baseline (T1), immediately after the intervention (T2), and at the 1-month (T3) and 3-month follow-up (T4). A total of 60 community-dwelling adults aged 18 to 60 years, with insomnia symptoms will be recruited in this study. All subjects will be computer randomized into either the active VeNS group or the sham VeNS group on a 1:1 ratio. All subjects in each group will receive twenty 30-min VeNS sessions during weekdays, which will be completed in a 4-week period. Baseline measurements and post-VeNS evaluation of the psychological outcomes (i.e., insomnia severity, sleep quality and quality of life) will also be conducted on all participants. The 1-month and 3-month follow-up period will be used to assess the short-and long-term sustainability of the VeNS intervention. For statistical analysis, a mixed model will be used to analyze the repeated measures data. Missing data will be managed by multiple imputations. The level of significance will be set to *p* < 0.05. Significance of the study: The results of this study will be used to determine whether this VeNS device can be considered as a self-help technological device to reduce the severity of insomnia in the community setting. We registered this clinical trial with the Clinical trial government, identifier: NCT04452981.

## 1. Introduction

Insomnia is one of the most common symptoms in the general population [1] and subpopulation in psychiatry, characterized by difficulty in falling asleep, maintaining sleep, and early morning awakening [2]. Insomnia can be acute, intermittent, or chronic and is often comorbid with physical and mental health conditions [3], such as decreased quality of life [4], hypertension [5], impaired immune system functioning [6], and cardiovascular disease [7]. Evaluating the symptoms of insomnia requires assessing, largely by history, whether an underlying condition can explain it. It is the diagnostic term for the symptoms of insomnia that merits specific attention. Cognitive behavioral therapy for insomnia is the preferred treatment approach because of its efficacy, safety, and durability of benefit, but pharmaceutical treatments are widely used for insomnia symptoms [3].

Insomnia is generally considered as a sleep disorder, characterized by a state of hyper arousal. Stress is believed to activate the hypothalamic–pituitary–adrenal (HPA) axis [8] and insomnia is often precipitated by stress in daily life [9]. Vestibular stimulation inhibits both the HPA axis and the sympathetic–adreno–medullar (SAM) axis and hence, decreases stress [10], excites sleep inducing areas such as the nucleus tractus solitarius (NTS) [11] and serotonergic dorsal raphe nucleus [12]. Vestibular stimulation also activates our midbrain. The activation of neurons in midbrain periaqueductal gray matter excites neurons of the rostral medulla and increases serotonin release. Activation of serotonin receptors causes the secretion of growth hormone-releasing hormone (GHRH) [13] which promotes rapid-eye movement and non-REM sleep in humans [14] which helps the modulation of sleep [15]. In addition, there is strong physiological evidence demonstrating that the vestibular system can affect REM sleep [16], and there is influence of labyrinthine inputs on the pontine reticular formation neurons involved in mediating switching between sleep states [17] and the medial vestibular nucleus has projections in regions mediating arousal, and some aspects of sleep will receive orexinergic inputs from the lateral hypothalamus [12]. Additionally, the electrical stimulation of the vestibular system can produce a rocking sensation which promotes sleep, as physical rocking is found to improve sleep in individuals with neuromuscular breathing problems [18], and the gentle swaying sensation produced by a vestibular device can significantly reduce sleep latency [19].

### 1.1. Prevalence of Insomnia in Different Countries

Insomnia co-exists with other common psychiatric disorders such as major depressive disorder, generalized anxiety disorder [20], and posttraumatic stress disorder [21]. In Hong Kong, the prevalence of insomnia in the general population was estimated at 11.9% [22] based on the presence of difficulty initiating sleep, difficulty maintaining sleep, or early-morning awakening occurring at least three nights per week in the past month. In mainland China, a study [23] found that the prevalence of any symptom of insomnia that occurred nearly every night for at least two weeks in the past year was 9.2%. In a Taiwan study, the prevalence of any insomnia symptoms that occurred either usually or all the time during the past month was 25.5% [24]. Another study showed that the prevalence of any insomnia symptoms that occurred almost every night for more than two weeks was 4.0% in Japan, 9.9% in South Korea, and 10.3% in Taiwan [25]. Although these studies have provided valuable data, owing to the differences in methodology and definition, the actual prevalence of insomnia in Asian countries remains unclear; hence, cross-cultural and cross-country comparisons are not possible [26].

### 1.2. Prevalence of Sleep Problems during COVID-19 Pandemic

The COVID-19 pandemic is an imminent public health emergency that has exacerbated or aggravated sleep disturbances in the Hong Kong community. Some researchers [27] investigated the prevalence and correlates of sleep disturbances during the early phase of the COVID-19 pandemic in Hong Kong using a web-based cross-sectional survey and convenience sampling. A total of 1138 Hong Kong adults were recruited over a two-week period in April 2020. The Insomnia Severity Index (ISI) was used to collect data on sleep disturbances, and other mood-related problems. The prevalence of insomnia (ISI score of ≥10) was 29.9%. Insufficient masks were significantly associated with worsened sleep quality; impaired sleep initiation and shortened sleep duration were significant correlates of insomnia (all *p*s < 0.05). Around 30–40% of participants reported that their overall sleep quality had worsened since the COVID-19 outbreak. Of particular note is that the prevalence of insomnia in Hong Kong has increased more than two-fold during the COVID-19 pandemic (11.9% in 2002 versus 29.9% in 2020).

### 1.3. Existing Treatment Modality for Insomnia and Past Research Findings

Medications are known to be effective in the treatment of primary insomnia in the clinical setting, but some individuals are reluctant to take the prescribed medications for fear of the drugs’ adverse effects. Psychotherapy such as cognitive behavioral therapy has also proven effective to treat insomnia but is often limited by the time and cost involved. Consequently, the majority of the individuals affected by sleeping disturbances did not seek professional help in the community in a timely fashion. Recent research findings suggested that complementary and alternative medicines (CAM) seemed to be one of the most preferred therapies for treatment of insomnia in Hong Kong, especially for the younger generations [28].

Another recent local pilot 3-armed RCT [29] examined the efficacy of integrated cognitive behavioral therapy (CBT) and acupressure in treating insomnia and its daytime impairments on 40 Chinese adults. Participants were randomly assigned to either the (1) integrated CBT with acupressure (CBTAcup) group (*n* = 14); (2) the CBT group (*n* = 13); or (3) the waitlist control (WL) group (*n* = 13). Linear mixed-effects models showed that both the CBTAcup and CBT groups had significantly lower insomnia severity (*d* = −1.74 and *d* = −2.61), dysfunctional beliefs related to sleep (*d* = −2.17 and −2.76), and mental fatigue (*d* = −1.43 and −1.60) compared with the WL group. The CBTAcup group also showed a reduction in total fatigue (*d* = −1.43) and physical fatigue (*d* = −1.45). Findings emerging from this study provided new empirical evidence to treat insomnia using integrated CBT-I and acupressure.

Insomnia is a known disorder of hyperarousal which can be attributed to increased activity in the frontal cortex during sleep. In other words, sleep disturbances have a bi-directional relationship with frontal metabolism during sleep. A recent prospective randomized controlled trial used frontal cerebral thermal therapy in 106 adults diagnosed with insomnia. Polysomnographic (PSG) was used to measure latency to persistent sleep and sleep efficiency. Results showed that two-night frontal cerebral thermal therapy improved patients’ abilities to fall asleep and had a benign safety profile [1].

### 1.4. Vestibular Stimulation

Vestibular stimulation is another alternative treatment option in the treatment and management of insomnia. A recent large-scale cross-sectional U.S. study (*n* = 20,950) found that vestibular function is closely associated with sleep quantity [30]. Results showed that 30% of individuals with vestibular vertigo reported abnormal sleep duration (15.5% short duration and 14.8% long duration). Individuals with vestibular vertigo had a higher relative risk ratio for abnormally short or long sleep duration. Further work is needed to evaluate the causal direction (s) of this association.

Modius Sleep (MS) is a non-invasive, transdermal neurostimulation device with a battery-powered headset designed to transcutaneously deliver low-level electrical current (0–1500 microamperes) to the subject’s head (neurostimulation) to treat insomnia. This MS delivers neurostimulation through two self-adhesive electrode pads which will be placed on the subject’s skin overlying each mastoid process behind the ear. MS delivers a small electrical impulse which can be (max. 1mA at 100 Hz) via Bluetooth using the mobile app to a level (0–10) where the subject can feel the tingling sensation in the skin (Table 1).

The subject will determine the level of neurostimulation once they begin to experience the gentle swaying indicating modulation of the vestibular nerve. This device will automatically turn off after 30 min of neuromodulation. The MS device will deliver a small electrical current onto the skin through the electrode pads. This electrical current serves as a neurosignaling waveform which modulates cranial nerves that influence the balance between the parasympathetic and sympathetic nervous systems. MS stimulates the head and vestibular nerves by Cranial Electrotherapy Stimulation (CES).

### 1.5. What Is Cranial Electrotherapy Stimulation (CES)? and Past Research Using CES on Insomnia 

Cranial electrotherapy stimulation (CES) has been approved by the U.S. Food and Drug Administration (FDA) for the treatment of insomnia [31]. CES is a non-invasive treatment using neuromodulation that applies alternating microcurrent transcutaneously to the human head via electrodes that can be placed on subjects’ earlobes, mastoid processes, zygomatic arches, or the maxilla–occipital junction [31]. One study [32] included 33 participants who received 4-week CES intervention, results showed that participants’ PSQI scores were significantly reduced in the post-stimulation (*p* = 0.002). More importantly, participants’ perceived level of anxiety (*p* = 0.001) and depression symptom scores (*p* = 0.024) also had a statistically significant reduction.

### 1.6. Objectives

The aim of this study is (1) to evaluate the efficacy of VeNS on insomnia severity on community-dwelling adults in Hong Kong and (2) to examine the association between VeNS data usage, insomnia severity, PSQI score, and quality of life.

### 1.7. Hypotheses

#### 1.7.1. Primary Hypothesis

Participants in the active VeNS group will have a statistically significant reduction in their (Insomnia Severity Index) (ISI) score after four weeks of treatment (T2), compared to the control participants. The effect will be maintained at 1-month (T3) and 3-months (T4) follow-up.

#### 1.7.2. Secondary Hypotheses

Higher data usage in the active VeNS group will be associated with larger improvement in insomnia severity, PSQI score, and quality of life after the 4-week treatment.

## 2. Materials and Methods

### 2.1. Trial Design

This is a two-armed, double-blind, randomized, sham-controlled trial evaluating the effects of a 4-week VeNS treatment on insomnia among Hong Kong adults in the general population. The study strictly complies with the Consolidated Standards of Reporting Trials (CONSORT) statement [33] and will be conducted in accordance with the Declaration of Helsinki [34] and Good Clinical Practice. Participants will be randomized into the active VeNS or sham VeNS group on a 1:1 ratio, balanced by their Insomnia Severity Index score, gender, and age. All the participants will be fully informed about the randomization procedures and that they have a 50% chance of receiving the active VeNS or the sham VeNS in this trial. Both groups will be measured at four time points: baseline (T1), immediately after the 4-week intervention (T2), at 1-month (T3), and 3-month follow-up (T4) (Figure 1).

### 2.2. Subjects

Samples will be recruited from our collaborative universities and NGO in Hong Kong. A flyer with registration QR code will be posted around the communal areas in the Hong Kong Polytechnic University (PolyU), University of Hong Kong (HKU), and the Chinese University of Hong Kong (CUHK). Email invitations with the QR code poster will also be sent to all staff/students and alumni across different faculties/departments at PolyU, HKU, and CUHK. A project poster will also be advertised with the School of Nursing, on PolyU Facebook, and Twitter.

### 2.3. Inclusion Criteria

To obtain a homogenous sample, the inclusion criteria will be (1) having an ISI score >15; (2) being ethnic Chinese aged 18–60 years; (3) able to understand/read Chinese; (4) currently not on prescribed or over-the-counter sleeping pills; (5) able to provide written informed consent; (6) having Wi-Fi and Bluetooth networks in iOS/Android mobile phones; (7) able to attend the face-to-face demonstration session for proper use of the MS device and return to the research assistants in the training venue (Integrative Health Clinic, School of Nursing, PolyU); (8) willing to engage with the project team on a weekly basis via WhatsApp/telephone to ensure compliance, proper usage of the MS device and report any technical issues; (9) not undergoing any extreme lifestyle changes that may impact on sleep quality (e.g., dietary changes/increase/decrease exercise levels) throughout the study period; (10) agreeing not using sleep trackers throughout the study period; and (11) not travelling to different time zones during the study period.

### 2.4. Exclusion Criteria 

Individuals with (1) a history of eczema/skin breakdown/other dermatological condition (e.g., psoriasis) affecting the skin behind the ears or having inner ear diseases; (2) HIV/AIDS infection (HIV will lead to vestibular neuropathy); and (3) use of beta-blockers/antidepressants/any other medications that may affect the neurostimulation; (4) history of stroke/epilepsy/severe head injury/neurosurgery; (5) active migraine with aura; (6) significant communicative impairments; (7) metal implant in brain or pacemaker, implanted defibrillator, deep brain stimulator, vagal nerve stimulator, etc.; (8) history of epilepsy; (9) pregnant or breastfeeding women; (10) cognitive impairment including Dementia/Alzheimer’s disease, and mild cognitive impairment; (11) history of major depressive disorder, psychotic disorder, bipolar affective disorder (depressive episode), or substance use disorders; (12) regular use of antihistamine medication in the last 6 months (because histamine receptors are present in the vestibular system); (13) history of malignancy in the past 12 months; (14) a diagnosis of myelofibrosis /myelodysplastic syndrome; (15) history of vestibular dysfunction or inner ear infections/diseases; (16) previous use of any VeNS device will be excluded.

### 2.5. Sample Size 

A recent pilot study [35] used electrical vestibular nerve stimulation on 20 adult participants with mild to moderate insomnia who were given fourteen 30-min electrical vestibular stimulation for two weeks. These sessions were delivered approximately 1 h prior to sleep onset. Results showed that participants’ ISI scores had a significant reduction after the VeNS (from mean ISI at baseline: 15.7 to mean ISI at 8.15, *p* < 0.00001).

Considering this trial is a sham-controlled trial, we hypothesize a large effect in the MS group. We used G*power version 3.1.9.7 (https://stats.oarc.ucla.edu/other/gpower/, accessed on 1 April 2022) to calculate the target sample size. With a statistical power of 95% and a statistical significance level at 0.05 to detect a large between-group effect size (Cohen’s *d*) of 0.8, each group will require 25 subjects. With an estimated attrition rate of 20% at 12-week posttreatment follow-up, we require 30 subjects per group, and hence, a total sample of 60 is required in this trial.

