## 3. Statistical Analyses

All statistical analyses will be performed by R for Windows (R version 4.1.0). Normal distribution of the data will be assessed by a Q-Q plot. Descriptive analysis that include means and standard deviations (SD) for the continuous variables will be presented, while numbers and percentages for the categorical variables will also be shown. A *p* value < 0.05 is considered statistically significant. Sociodemographic differences between the active VeNS group and the sham VeNS group will be analyzed using Chi-square test and *t* test. Should there be significant differences in sociodemographic factors between the two groups, covariates will be considered as confounding variables in the statistical analyses. Normality of the primary outcome (ISI) scores will be tested by the Shapiro–Wilk test. The independent samples *t* test will be used to test the baseline difference between the two groups.

A mixed model will be used to test the group (between-subject factor), time (within-subject factor), and group × time interaction effects of the ISI score between the active VeNS group and the sham VeNS group. Post hoc comparisons between groups and time points will be conducted using a *t* test with Bonferroni correction. A Cohen’s *d* effect size for each outcome will be calculated, where *d* = 0.2, 0.5, and 0.8 correspond to small, medium, and large effect size. Participants’ total usage time will also be used to investigate the effectiveness of the VeNS on anxiety and total usage time will be used as a continuous covariate in a linear regression model for ISI total score. Missing data will be managed by multiple imputation [45] by adopting the last observation carried forward (LOCF) method.

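### The stated 95% power for d = 0.8 with 25 per group is wrong: a two-sided t-test gives about 79%, and about 77% with the 24 per group left after 20% attrition

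*Protocol article*

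**What the plan says.** Section 2.5 (Sample Size) of the protocol article says that G*Power was used and gives the inputs: "With a statistical power of 95% and a statistical significance level at 0.05 to detect a large between-group effect size", with Cohen's d "of 0.8, each group will require 25 subjects". It then allows for dropout: "With an estimated attrition rate of 20% at 12-week posttreatment follow-up, we require 30 subjects per group", and concludes that "a total sample of 60 is required in this trial".

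Section 2.1 gives the allocation: "Participants will be randomized into the active VeNS or sham VeNS group on a 1:1 ratio". Section 1.7.1 places the primary comparison, active against sham on the ISI, at T2 (after four weeks of treatment), and adds that the effect will be maintained at T3 and T4. Section 3 plans a mixed model with group, time and their interaction, and sets the criterion: "A *p* value < 0.05 is considered statistically significant". Neither section states whether the test is one- or two-sided. Section 2.5 does not name the G*Power procedure, a correlation or a number of repeated measurements.

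**The concern.** Power, alpha, effect size and allocation together determine the sample size of a two-group comparison, up to sidedness. All of them are printed, so the 25 can be checked, and it looks far too small for 95% power at d = 0.8; it is close to the familiar answer for 80% power. The inflation for dropout also looks like multiplication by 1.2 where division by 0.8 is needed.

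What is at stake is how a negative result can be read. A trial with 95% power for d = 0.8 has a 5% chance of missing an effect of that size, so a null result would count heavily against the device. If the chance is really above 20%, the same result says much less.

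**Working it through.** **Inputs.** d = 0.8, alpha = 0.05, power 0.95, 25 per group, attrition 20%, 30 per group randomised (all section 2.5); allocation 1:1 (section 2.1). Sidedness is not stated, so both versions are computed.

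**Method.** Two-sample t-test with the noncentral t distribution. With n per group, df = 2n − 2 and noncentrality = d × √(n/2). Two-sided power is the probability that |T| exceeds the 97.5% point of t; the one-sided version uses the 95% point.

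**Step 1: try to reproduce 25 at 95% power.** At n = 25, noncentrality = 0.8 × √12.5 = 2.828, df = 48 and the two-sided critical value is 2.011. Power is 79.1%. One-sided it is 87.4%. The figure does not reproduce either way.

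**Step 2: sample size that 95% power needs.**

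- Two-sided: 41 per group gives 94.7% and 42 gives 95.2%, so 42.
- One-sided: 34 per group gives 94.7% and 35 gives 95.2%, so 35.
- Normal approximation, two-sided: n = 2 × (1.960 + 1.645)² / 0.8² = 40.6, so 41.

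**Step 3: where 25 might come from.** The normal approximation for 80% power is n = 2 × (1.960 + 0.842)² / 0.8² = 24.5, rounded up to 25. The exact t-test for 80% needs 26 (25 gives 79.1%, 26 gives 80.8%). The match is suggestive but is not proof of origin.

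**Step 4: attrition.**

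- Correct inflation: 25 / (1 − 0.20) = 31.25, so 32 per group.
- The plan's 30 equals 25 × 1.2.
- Check: 30 × 0.80 = 24, one fewer per group than the stated requirement.

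**Step 5: power at the sizes that matter (d = 0.8, unadjusted t-test).**

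| Evaluable per group | Two-sided | One-sided |
|---|---|---|
| 24 (after 20% loss) | 77.4% | 86.1% |
| 25 (stated requirement) | 79.1% | 87.4% |
| 30 (no loss) | 86.1% | 92.2% |

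No cell reaches 95%.

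**Step 6: effect that the design does detect with 95% power.** Solving for d, two-sided, gives 1.04 with 25 per group and 1.06 with 24.

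**Step 7: other models, with a correlation assumed because none is stated.**

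- Baseline-adjusted comparison at T2: the effective effect size is 0.8 / √(1 − r²). With r = 0.5 it is 0.924, and two-sided power is 89% at 25 per group and 88% at 24. With r = 0.6 it is 1.0, and power is 93% and 92%. With r = 0.7, power is 97% at both sizes.
- Repeated-measures ANOVA, between-group effect averaged over four visits (f = 0.4): at 50 in total, power is 96.2% with a correlation of 0.4 and 93.9% with 0.5; the latter needs 54 in total for 95%.

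**The case against.** The planned analysis is a mixed model over four visits, not a t-test at one visit, and the G*Power procedure is unnamed. As step 7 shows, some repeated-measures or baseline-adjusted calculations come close to or pass 95% with 25 per group. The 25 may come from one of these, and calling any single number the true power would then go too far. This stands as a reason to ask which procedure was used. It does not rescue the text: section 2.5 states a between-group Cohen's d and gives no correlation, and the four-visit average folds baseline into the group effect, which is not the T2 contrast of the primary hypothesis.

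The 20% attrition is set for the 12-week follow-up, while the primary comparison is first made at T2, where loss should be no greater, and section 3 plans imputation. So 77% is the low end for T2, and two-sided unadjusted power there lies between 77% and 86%. That is a fair limit, but the primary hypothesis also covers T3 and T4, and even zero loss falls short of 95%.

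A one-sided test would raise the figures to 86–92%, again below 95%.

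The attrition slip is small by itself: one evaluable participant per group, or 79.1% against 77.4%. It is secondary to the power figure. The document also does not say how a null result would be interpreted, so the risk of over-reading one is an inference from the claimed power.

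**Conclusion.** The concern holds. The power, alpha, effect size and sample size printed in section 2.5 are mutually inconsistent under a two-sample comparison, whichever sidedness is meant. For a two-sided unadjusted t-test, power at d = 0.8 is 79.1% with 25 per group and 77.4% with 24, so the chance of missing such an effect is about 21–23%, not 5%. Across one- or two-sided tests and 24 to 30 evaluable per group, unadjusted power runs from 77% to 92%. The 77% assumes that the full 20% is lost by the visit analysed and that those participants contribute nothing. A figure of 95% would need a correlation and a procedure that the section does not give. Separately, 30 per group does not protect 25 evaluable against 20% loss; 32 would. Because this is a stated figure on which the trial's size rests, it must be corrected.

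**What to change.** Keep 60 participants and restate the justification, for example: 60 randomised, about 24 per group evaluable after 20% attrition, gives about 77% power (two-sided alpha 0.05) for d = 0.8 by an unadjusted t-test, and about 86% with no attrition. State the sidedness explicitly; the sponsor should confirm that two-sided is meant. Show the attrition step as n / (1 − 0.20).

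If the original calculation used a different G*Power procedure, name it, give its assumed correlation and number of measurements, and show that it addresses the T2 contrast. If the primary analysis is to be baseline-adjusted, quote the adjusted power with its assumption, for example about 88% with 24 per group and a correlation of 0.5.

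This costs wording only, with no extra participants, but the stated power becomes less favourable. Keeping the 95% claim with an unadjusted two-sided t-test would instead need 42 evaluable per group: 42 / 0.80 = 52.5, so 53 per group and 106 randomised.
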